### 18.2 Secondary Efficacy Endpoints

The secondary analysis variables are listed below

- Clinical response at Day 4 (mMITT and CE analyses sets)
- Investigator determined Clinical outcome at EOT (MITT, mMITT and CE analyses sets)
- Investigator determined Clinical outcome at TOC (MITT, mMITT and CE analyses sets)
- Hospitalisation prior to FU (MITT analyses set)
- By-pathogen clinical response at Day 4 and by-pathogen clinical outcome at TOC (mMITT analyses sets)

#### *Investigator determined Clinical Outcome at EOT (MITT, mMITT and CE Analyses Sets)*

- Clinical Cure: Alive and signs and symptoms of CABP (dyspnoea, production of purulent sputum or pleuritic chest pain) are resolved or return to premorbid conditions and cough is improved such that further antibacterial therapy is no needed and the subject otherwise cannot be declared a clinical failure.
- Clinical Failure: The signs and symptoms of CABP (dyspnoea, production of purulent sputum or pleuritic chest pain) did not resolve or return to premorbid and/or cough worsened, such that non-study antibacterial therapy must be initiated for the treatment of CABP or death occurred prior to assessment or subject received alternative anti-microbial therapy for the treatment of CABP prior to this visit.

[figure not shown]

- Indeterminate: Study data are missing for the evaluation of efficacy at the assessment visit for any reason, including loss to FU.

### ***Investigator determined Clinical Outcome at TOC (MITT, mMITT and CE Analyses Sets)***

- Clinical Cure, Clinical Failure or Indeterminate: Definitions are as above. Failures at EOT will be carried forward to TOC.

### ***Hospitalisation Prior to FU (MITT Analyses set)***

- Hospital re-admission for any reason between the Day 1 and the FU visits, if previously hospitalised and discharged or initial hospital admission for any reason between the Day 2 and the FU visits (Day 31  $\pm$  4 days), if not previously hospitalised on Day 1.

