### **5.2 SECONDARY OBJECTIVES**

- To assess the clinical response at Day 4 in the Microbiological Modified Intent-to-Treat (mMITT) and Clinically Evaluable (CE) analyses sets
- To assess the clinical outcome at End of Treatment (EOT) in the MITT, mMITT and CE analyses sets
- To assess the clinical outcome at Test of Cure (TOC) in the MITT, mMITT and CE analyses sets
- To assess re-admission to the hospital (or admission to the hospital if not previously hospitalised) for any reason before Follow-Up (FU) (Day 31  $\pm$  4 days) in the MITT analyses set
- To determine the PK of oral nafithromycin (in PK analysis set)
- To assess by-pathogen clinical response at Day 4 and by-pathogen clinical outcome at TOC in the mMITT analyses set

[figure not shown]

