- Subjects with polymicrobial infections due to Gram-positive pathogens only
- Subjects with polymicrobial infections due to Gram-negative pathogens only
- Subjects with polymicrobial infections due to atypical pathogens only
- Subjects with polymicrobial infections due to typical pathogens only of the same Gram type
- Subjects with mixed Gram-positive and Gram-negative Infections
- Subjects with mixed Gram-positive and Gram-negative Infections without atypical pathogens

The by-pathogen favourable clinical response at Day 4 and also the by-pathogen clinical cure rate at TOC will be summarized in the mMITT analyses set.

In the by-pathogen summaries, typical pathogens will be categorized as Gram-negative-fastidious, Gram-negative non-fastidious and Gram-positive.

The by-pathogen favourable clinical response at Day 4 and also the by-pathogen cure rate at TOC will also be summarized in the mMITT analyses set for:

- Subjects with monomicrobial infections due to typical pathogens
- Subjects with monomicrobial infections due to atypical pathogens
- Subjects with polymicrobial infections
  - Subjects with polymicrobial infections due to typical pathogens only
  - Subjects with polymicrobial infections due to typical and atypical

[figure not shown]

pathogens

- Subjects with polymicrobial infections due to atypical pathogens only

The incidence of superinfections and new infections will be summarized and listings by pathogen will be provided for each treatment group. In addition, subjects in the mMITT analyses set, whose baseline pathogen(s) has a decreased susceptibility (defined as a 4-fold increase in the baseline MIC) to the study treatment received in a post-baseline culture will be listed.

An assessment of hospitalisation (defined as re-admission to the hospital if previously hospitalised on or after study drug initiation [Day 1] and before FU or initial hospital admission [if not previously hospitalised] for any reason between the initiation of the study drug (Day 1) and before FU will be summarized using frequency and percentage for subjects in MITT analyses set.

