### Partial Date

Missing day - Impute the last day of the month unless month is same as month of first dose of study drug then impute last dose date.

Missing day and month – Impute 31st December unless year is the same as first dose date then impute last dose date.

Note: For the purpose of displaying related events, events with relationship marked as “Missing” relationship will be considered as “Treatment Related”.

In case the AE end date is missing, the AE will be kept as ‘ongoing’. The duration of AE in the listing will be displayed as >xx days. Here xx days means the total duration in days from the date when the AE started till the end of the study.

Missing times, severity and causality for AEs will be queried for a value. No imputations will be made for missing times. AEs with a missing time will be considered treatment emergent if the date is on or after the first dose of the study drug, AEs with missing severity will be considered severe and AEs with a missing relationship to the study drug will be considered related to the study drug.

- For the primary efficacy outcome at Day 4, subjects with missing data will be considered Indeterminate response. By definition, subjects with Indeterminate response will be included in the denominator for analyses in the MITT analyses set.
- Missing values for other efficacy outcomes will be handled in a similar manner as the primary efficacy outcome.
- For evaluations at the TOC Visit, subjects with Indeterminate response will be included in the denominator for analyses in the MITT analyses set and will be excluded from the CE analyses set at TOC.

[figure not shown]

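### The hospitalisation endpoint has two start days for an initial admission (Day 2 and Day 1), and the borrowed missing-data rule does not settle how loss or death before follow-up enters its rate

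*SAP*

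**What the plan says.** Hospitalisation before follow-up (FU, Day 31 ± 4 days) is a listed secondary endpoint in the MITT set, and the SAP describes it in several places.

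- **Section 5.2** sets the objective as admission or re-admission "for any reason before Follow-Up (FU". It gives no start day.
- **Section 18.2** has two branches. The first is "Hospital re-admission for any reason between the Day 1 and the FU visits", for subjects already hospitalised and discharged. The second is "initial hospital admission for any reason between the Day 2 and the FU visits", which applies "if not previously hospitalised on Day 1".
- **Section 19.3** defines the endpoint again: "re-admission to the hospital if previously hospitalised on or after study drug initiation [Day 1] and before FU", or an initial admission "for any reason between the initiation of the study drug (Day 1) and before FU". It is to be summarised as a frequency and percentage of MITT subjects. Table 2 in the same section labels the variable as a rate of re-admission.
- **Section 19.3** also states generally that the confidence interval for each secondary outcome is for the difference in the proportion with a favourable response.
- **Section 23** says of the primary outcome that "subjects with Indeterminate response will be included in the denominator for analyses in the MITT analyses set", and then: "Missing values for other efficacy outcomes will be handled in a similar manner as the primary efficacy outcome".

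**The concern.** Two things are left open in one endpoint.

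First, Sections 18.2 and 19.3 should describe the same event but start the clock for an initial admission on different days. Two programmers following the two sections could produce different counts.

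Second, keeping missing subjects in the denominator is conservative only when the numerator is a good outcome. Section 19.2 makes this explicit for the primary endpoint: missing subjects then count as unfavourable. When the numerator is admissions, the same rule puts a lost subject among those not admitted. An arm with more losses would then tend to show a lower admission rate. The only text pointing the other way is the general favourable-response wording in Section 19.3, and no favourable category is defined for hospitalisation. Death is also left open: a subject who dies without being admitted does not meet either event definition, and no rule says how that subject is counted.

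**Working it through.** **Start day.** The definitions side by side:

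| SAP section | Re-admission | Initial admission |
|---|---|---|
| 5.2 | before FU, no start day | before FU, no start day |
| 18.2 | Day 1 to FU | Day 2 to FU, if not in hospital on Day 1 |
| 19.3 | study drug start (Day 1) to before FU | study drug start (Day 1) to before FU |

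The re-admission start agrees. Only the initial-admission start differs, and the subject affected is one who is out of hospital at first dose and admitted later the same day. Section 5.2 cannot decide between the two, and the list of changes from the protocol in Section 26 does not mention hospitalisation. At 207 per arm, each such subject moves an arm's rate by 1/207 = 0.48 points.

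**Death.** Section 18.1 makes death by Day 4 unfavourable. The EOT outcome in Section 18.2 makes death before assessment a failure, and EOT failures carry forward to TOC. The hospitalisation definitions in 18.2 and 19.3 contain no such clause.

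**Missing data.** The SAP gives no figure for admissions or for loss by FU. Its only dropout figure is at most 5% by Day 4 (Section 9). What follows is an illustration on assumed counts.

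The denominator comes from Section 9 and reproduces: (1.960 + 1.282)² × 2 × 0.81 × 0.19 / 0.125² = 207 per arm, 414 in total, and 414/0.85 = 487.06, rounded up to 488 enrolled. A restricted-likelihood version gives 211 per arm; nothing here depends on that difference.

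Assume 207 per arm, 10 observed admissions in each arm, and 10, 20 or 30 subjects in arm 1 against 10 in arm 2 not observed to FU. Three treatments of the unobserved:

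- A: kept in the denominator, not in the numerator: 10/207.
- B: observed subjects only: 10/(207 − lost).
- C: counted as not favourable: (10 + lost)/207.

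| Lost, arm 1 v arm 2 | A | B | C |
|---|---|---|---|
| 10 v 10 | 4.8% v 4.8%, 0.0 | 5.1% v 5.1%, 0.0 | 9.7% v 9.7%, 0.0 |
| 20 v 10 | 4.8% v 4.8%, 0.0 | 5.3% v 5.1%, +0.3 | 14.5% v 9.7%, +4.8 |
| 30 v 10 | 4.8% v 4.8%, 0.0 | 5.6% v 5.1%, +0.6 | 19.3% v 9.7%, +9.7 |

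Miettinen-Nurminen 95% intervals: A, −4.4 to 4.4 in every row; C, −1.5 to 11.3 for 20 v 10 and 2.9 to 16.6 for 30 v 10.

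Reading A follows from an event percentage over all MITT subjects (Table 2, the summary sentence in 19.3, and Section 23). Reading C follows from the favourable-response interval in 19.3 combined with the effect described in 19.2. The SAP can be read either way. With equal losses the difference does not move, although the reported level doubles from 4.8% to 9.7%.

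**The case against.** The start-day conflict is narrow. It touches one branch, and probably few subjects are admitted on Day 1 after an outpatient first dose. That is fair as to size, but it does not remove the contradiction.

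On missing data, the SAP nowhere says that a lost subject counts as not hospitalised. Section 23 asks for handling similar to the primary, Section 19.2 says the primary rule counts missing as unfavourable, and Section 19.3 puts the interval on favourable response. Taken together, these support the conservative reading. This stands to the extent that the SAP cannot be said to prescribe the lenient reading. It does not make the text clear, because the endpoint is named and summarised as an event rate and its favourable category is never defined.

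A reader might also infer that the missing-data rule scores deaths as good outcomes. The SAP does not support this. A known death is not a missing value, so Section 23 does not govern it; the gap is in the endpoint definition. Deaths before EOT or TOC assessment already count as failures in the clinical outcome, and serious adverse events are recorded to FU. An admission endpoint without death is a legitimate choice that matches the objective in Section 5.2, so replacing it with a composite would change the objective, not correct an error.

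Finally, this is one secondary endpoint with no margin or stated hypothesis. The primary conclusion is unaffected.

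**Conclusion.** The point holds in two parts. The start day for an initial admission contradicts itself between Sections 18.2 and 19.3; this is textual and needs no assumption. The handling of loss and death before FU is not defined for this endpoint, and the rule borrowed from the primary reverses its direction if applied to the admission rate as reported.

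The size cannot be fixed from the SAP. On the assumed counts, the choice of reading moves the arm difference by 0 points with equal losses, 4.8 points with 20 v 10 lost, and 9.7 points with 30 v 10 lost. It would be tempting to conclude that the plan favours one arm. Nothing in the SAP shows that: the difference between arms changes only if losses or deaths are unequal, and no figure suggests that they will be. The matter should be settled before unblinding, in proportion to a secondary endpoint.

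**What to change.** 1. Reconcile Sections 18.2 and 19.3 to one start day for an initial admission, checked against the protocol, and use the same sentence in both. The SAP alone does not show which day was intended.
2. Keep admission or re-admission as the endpoint. Define its favourable category as known not to have been admitted or re-admitted through FU, with unknown status not counted as favourable, so that the interval in Section 19.3 can be computed.
3. Tabulate admitted, not admitted and unknown separately by arm, so that the effect of the rule is visible.
4. Add a supportive analysis of being alive and not admitted or re-admitted through FU, with death as an event. State in the main definition how a death without admission is counted.

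The cost is SAP wording, one derivation and one extra table. The downside is that the unfavourable proportion rises by the share with unknown status, which may exceed the admission rate itself. In the illustration, 10 lost subjects raise it from 4.8% to 9.7%, and 20 raise it to 14.5%. Showing the three categories separately keeps the admission rate readable.

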### ***By-Pathogen Clinical Response at Day 4 and By-Pathogen Clinical Outcome at TOC in the mMITT Analysis Set***

The by-subject clinical response at Day 4 and clinical outcome at TOC defined above will be applied to each pathogen to obtain the:

- By-pathogen favorable Response at Day 4 (definitions as mentioned above)
- By-pathogen cure rate at TOC: (definitions as mentioned above)

## **18.3 Safety Endpoints**

- Incidence of treatment-emergent adverse events (TEAEs), serious adverse events (SAEs) and discontinuations due to TEAEs
- Incidence of potentially clinically significant (PCS) changes in safety laboratory parameters, vital signs and electrocardiograms (ECGs)

[figure not shown]

## 19. EFFICACY ANALYSES

Except for the safety analyses set, subject data will be analysed in the treatment group to which the subject was randomised. For the safety analyses set, subject data will be analysed according to the treatment group that the subject actually received.

### 19.1 Primary Efficacy Analysis

The primary efficacy endpoint for this study is the proportion of subjects with favourable clinical response at Day 4 in the MITT analyses set. Subjects will be categorised as having Favourable, Unfavourable or Indeterminate response. Subjects with missing data or who are lost to follow-up (FU) are defined as Indeterminate and will be included in the denominator for the calculation of the proportion of subjects with Favourable clinical response at Day 4.

The number and percentage of subjects in each treatment group and in each response category will be reported.

The null ( $H_0$ ) and alternative ( $H_1$ ) hypotheses are the following:

$$H_0: \pi_1 - \pi_2 \leq -0.125 \text{ vs. } H_1: \pi_1 - \pi_2 > -0.125$$

Where:

$\pi_1$  = the proportion of subjects with favourable clinical response at Day 4 in the nafithromycin treatment group

$\pi_2$  = the proportion of subjects with favourable clinical response at Day 4 in the moxifloxacin treatment group

The non-inferiority hypothesis test is a 1-sided hypothesis test performed at the 2.5% level of significance. The statistical test is based on the lower limit of the 2-sided 95% CIs for the observed difference in the proportion of subjects with favourable clinical response at Day 4 (nafithromycin minus moxifloxacin). The CI will be obtained using the method of Miettinen and Nurminen.

If the lower limit of the 2-sided 95% CI for the difference between treatment groups (nafithromycin minus moxifloxacin) in the proportion of subjects with favourable clinical response rates at Day 4 in the MITT analyses set is greater than  $-0.125$ , the null hypothesis  $H_0$  will be rejected in favour of the alternative hypothesis  $H_1$  and the non-inferiority of nafithromycin monotherapy to moxifloxacin will be concluded. In addition, if the lower limit of the 2-sided 95% CI for the difference between treatment groups (nafithromycin minus moxifloxacin) in the proportion of subjects with favourable clinical response rates at Day 4 is greater than zero, the superiority of nafithromycin monotherapy to moxifloxacin monotherapy will also be concluded.

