**7. RANDOMISATION**

Subjects will be randomised using block randomisation, stratified by Pneumonia Outcomes Research Team (PORT) Risk Class (II vs. III/IV) to avoid bias while assigning the treatment arm. Subjects will be randomly assigned in blinded manner to 1 of the 2 treatment arms using an Interactive web recognition system (IWRS) in the ratio of 1:1. Enrolment of Pneumonia Outcome Research Team (PORT) Risk Class II will be capped at 60% and enrolment of subjects with allowed prior systemic antibiotic use will be capped initially at 25% (subject to change during study conduct).

[figure not shown]

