### 19.2 Sensitivity Analysis

The following sensitivity analyses for the primary efficacy outcome will be conducted:

[figure not shown]

1. Comparison of the clinical response rates at Day 4 between treatment groups in the MITT analyses set using the Miettinen-Nurminen statistic stratified by the randomisation factor: PORT Risk Class: I (ineligible for study), II (eligible), III (eligible), IV (score of 91-105 eligible and 106-130 ineligible) and V (ineligible for study). Stratum classes for PORT score are II and III/IV.
2. Subjects with missing data will be considered to have an Indeterminate response. By definition, subjects with indeterminate response will be included in the denominator for analyses in the MITT analyses set effectively counting these as unfavorable responses. A sensitivity analyses in which subjects with Indeterminate outcome in the MITT analyses set are imputed as having a favourable response will also be conducted using the same statistical methods as for the primary analysis.

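### Randomisation is stratified by PORT Risk Class but the primary interval is not; making the planned stratified interval primary is a small, cheap gain if PORT class predicts response

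*SAP*

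**What the plan says.** Section 7 describes block randomisation "stratified by Pneumonia Outcomes Research Team (PORT) Risk Class (II vs. III/IV"), carried out "using an Interactive web recognition system (IWRS) in the ratio of 1:1". It also limits the mix of classes: "Enrolment of Pneumonia Outcome Research Team (PORT) Risk Class II will be capped at 60" per cent.

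Section 19.1 sets the decision rule: "The non-inferiority hypothesis test is a 1-sided hypothesis test performed at the 2.5% level of significance", read from the lower limit of the two-sided 95% interval for nafithromycin minus moxifloxacin. On how that limit is obtained it says only "The CI will be obtained using the method of Miettinen and Nurminen". The same interval serves both the -0.125 threshold and the superiority threshold of 0.

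Section 19.2 lists as its first sensitivity analysis a comparison "using the Miettinen-Nurminen statistic stratified by the randomisation factor", and adds: "Stratum classes for PORT score are II and III/IV". Set against this, the primary interval is plainly meant to be unstratified. No stratum weights are given.

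Section 9 sizes the MITT set at 414 (207 per arm) by the Farrington-Manning approach, also without strata.

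**The concern.** Stratified allocation largely removes chance imbalance in PORT class between the arms. If PORT class predicts response, the difference in proportions then varies less from trial to trial than an unstratified variance formula assumes. The lower confidence limit, on which the non-inferiority decision rests, then lies slightly further down than the design requires. The SAP treats PORT class as important throughout: it stratifies on it, caps one class, counts randomisation in the wrong stratum as a significant deviation (Section 14, Table 1) and uses it as a subgroup (Section 19.4). It gives no reason for leaving it out of the primary interval. At stake is a little precision, not the validity of the conclusion.

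**Working it through.** **Inputs from the SAP.** 207 per arm in the MITT set, 81% attained response in both arms, margin 0.125, one-sided 2.5% (Sections 9 and 19.1); two strata, 1:1 allocation, PORT II at most 60% (Section 7).

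**Assumed, because the SAP is silent.** The gap in response between PORT II and III/IV, taken from 0 to 20 points; PORT II exactly at its 60% cap; allocation balanced within strata.

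**1. The plan's own figures.** With unpooled variance, n per arm = (1.960 + 1.2816)² × 2 × 0.81 × 0.19 / 0.125² = 10.507 × 0.3078 / 0.015625 ≈ 207, so 414 in total, as stated. Enrolment is 414 / 0.85 = 487.1, rounded up to 488, as stated. With the restricted null variance (restricted rates 0.733 and 0.858) the Farrington-Manning formula needs 211 per arm and gives 89.4% power at 207.

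**2. Variance removed by stratifying.** Ratio = [0.6·p₂(1−p₂) + 0.4·p₃(1−p₃)] / [0.81 × 0.19], where p₂ and p₃ are the response rates in PORT II and III/IV.
- 10-point gap (85% and 75%): (0.0765 + 0.0750) / 0.1539 = 0.984; standard error ratio 0.992.
- 20-point gap (89% and 69%): (0.0587 + 0.0856) / 0.1539 = 0.938; standard error ratio 0.968.

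These simple ratios overstate the gain for the planned method, so the Miettinen-Nurminen intervals were computed directly.

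**3. Miettinen-Nurminen 95% intervals**, observed difference 0, stratum weights n₁n₂/(n₁+n₂). The unstratified half-width is 0.0762 in every row.

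| Gap (points) | PORT II / III-IV | Stratified half-width | Width relative to unstratified |
|---|---|---|---|
| 0 | 81 / 81% | 0.0763 | 1.0012 |
| 5 | 83 / 78% | 0.0761 | 0.9997 |
| 10 | 85 / 75% | 0.0758 | 0.9948 |
| 15 | 87 / 72% | 0.0752 | 0.9867 |
| 20 | 89 / 69% | 0.0743 | 0.9754 |

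The slight widening at no gap comes from the N/(N−1) factor, which is applied within each stratum. The weighted factor is 0.6 × 248.4/247.4 + 0.4 × 165.6/164.6 = 1.0048, against 414/413 = 1.0024, and the square root of their ratio is 1.0012. A 50/50 split of PORT classes gives nearly the same table (0.9946 at 10 points, 0.9755 at 20).

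**4. Operating characteristics**, 40,000 simulated trials per scenario with 124 and 83 per arm in the two strata. Power is at a true difference of 0; type I error is at a true difference of -0.125 in each stratum (68.5% against 81% overall).

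| Gap (points) | Power, unstratified | Power, stratified | Type I, unstratified | Type I, stratified |
|---|---|---|---|---|
| 0 | 89.7% | 89.8% | 0.0234 | 0.0234 |
| 10 | 90.0% | 90.2% | 0.0256 | 0.0261 |
| 20 | 90.5% | 91.1% | 0.0212 | 0.0245 |

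The Monte Carlo standard error of the type I figures is about 0.0008. At gaps of 0 and 10 points all four are compatible with 0.025. At 20 points the unstratified test leaves part of its 2.5% unused.

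**The case against.** The SAP is coherent as it stands. It fixes one primary method, sizes the trial by the matching unstratified approach, and commits to reporting the stratified result as well. Which of two valid, pre-specified analyses is called primary is partly a matter of preference. Section 26 lists the departures from the protocol and the primary interval is not among them, which suggests that the unstratified method follows the protocol; the protocol itself was not available for this check. Section 20.2 speaks of coagulation data in the past tense, so data collection was probably well advanced. Changing the primary method at that stage for less than one point of power has some cost in credibility. All of this stands, and it is why the point is minor.

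A reader might infer more than the document supports:
- **That the primary interval is simply too wide.** That needs a response gap between PORT classes, and the SAP gives none. At 0 to 5 points there is practically no difference.
- **That the unstratified test is wrong or could favour a false non-inferiority claim.** The simulations show a valid test that is at most mildly conservative.
- **That the trial needs this change to reach its power.** In the scenarios where stratifying helps, the unstratified test already has 90.0% and 90.5% power. The 89.4% in step 1 ignores the stratified allocation and belongs to the sample-size section.

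What remains is that the design already includes the stratification and the analysis that uses it is already planned.

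**Conclusion.** The point holds as a minor improvement in efficiency and in agreement with the design. Under 60% in PORT II and 81% response overall, moving to the stratified interval changes the half-width by between +0.1% and -2.5% as the gap goes from 0 to 20 points. The lower limit moves by at most 0.0762 − 0.0743 = 0.0019, against a margin of 0.125, and power rises by about 0 to 0.6 points. Everything rests on the assumed gap, for which the SAP gives no figure. The SAP neither contradicts itself nor errs here.

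One related gap matters whichever analysis is primary. Section 19.2 does not state the stratum weights, nor whether a subject randomised in the wrong stratum, a case that Section 14 foresees, is analysed by the stratum as randomised or by actual PORT class.

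**What to change.** Before unblinding:
1. In Section 19.1, make the PORT-stratified Miettinen-Nurminen 95% interval primary for both the -0.125 and the 0 threshold. Use the two strata (II, III/IV) as randomised and state the weights, for example n₁n₂/(n₁+n₂) per stratum.
2. In Section 19.2, keep the unstratified interval as a sensitivity analysis.
3. Sections 19.2 (the analysis counting Indeterminate as favourable) and 19.3 (by-subject secondary endpoints) refer back to the primary method. State whether they follow the change; no gain was computed for the smaller mMITT and CE sets.
4. Record the change and its reason in Section 26.

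The cost is a few lines of text and no new data or sample size, since a stratified analysis is already planned. The downside is a change of the pre-specified primary method and an interval about 0.1% wider if PORT class turns out not to be prognostic. If the sponsor prefers to keep the present order, the weights and the stratum definition should still be added to Section 19.2.
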